## Abstract

**Background:**

Interoception—the perception and integration of internal bodily signals—is fundamental to emotion regulation, bodily self-awareness, and predictive coding. Emerging evidence suggests that interoceptive disturbances may contribute to core psychopathological features of schizophrenia. Our research group recently conducted a systematic review and meta-analysis demonstrating significant impairments in interoceptive accuracy and sensitivity among individuals with schizophrenia. However, the neural mechanisms underlying these deficits remain unclear.

**Methods:**

This cross-sectional protocol will recruit 30 individuals with schizophrenia and 30 age- and sex-matched healthy controls. Participants will complete (1) behavioral interoceptive assessment using the heartbeat counting task; (2) subjective interoceptive questionnaires, including the Multidimensional Assessment of Interoceptive Awareness (MAIA) and the Body Perception Questionnaire (BPQ); (3) clinical symptom ratings (PANSS, HAM-A, HAM-D); and (4) cognitive testing (TMT, animal fluency, DSST). All participants will undergo multimodal MRI scanning, including structural T1-weighted imaging, resting-state fMRI, and diffusion tensor imaging. Neuroimaging data will be preprocessed and analyzed using DPABISurf, SPM12, and GRETNA. Expected Results: We anticipate that individuals with schizophrenia will show reduced interoceptive accuracy, altered subjective interoceptive awareness, and abnormal intrinsic neural activity and connectivity within interoception-related circuits, including the anterior insula, anterior cingulate cortex, amygdala, and thalamus. Structural abnormalities within thalamo-cortical pathways are also expected. Interoceptive deficits are hypothesized to correlate with symptom severity and cognitive performance.

**Conclusions:**

This study will provide an integrated characterization of interoceptive dysfunction and its neural correlates in schizophrenia. Findings may advance understanding of bodily self-disturbance and emotional dysregulation and support the development of future interoception-focused therapeutic approaches.

**Clinical trial registration:**

https://www.chictr.org.cn/, identifier ChiCTR2500110551.

## Introduction

1

Schizophrenia spectrum disorders are heterogeneous psychiatric conditions characterized by positive symptoms (e.g., hallucinations and delusions), disorganized thinking or behavior, and negative symptoms such as diminished emotional expression and avolition, accompanied by varying degrees of cognitive and functional impairment. Epidemiological studies estimate a lifetime prevalence of schizophrenia spectrum disorders of approximately 0.3–0.7%, although estimates vary across populations and geographic regions. Individuals with schizophrenia spectrum disorders have a reduced life expectancy compared with the general population, reflecting a combination of physical health comorbidities, lifestyle factors, and healthcare disparities (1, 2). These conditions are associated with challenges in emotional regulation, cognitive functioning, and social participation, particularly given their typical onset in early adulthood and recurrent symptom fluctuations, highlighting the importance of improving mechanistic understanding and clinical care (3). Although considerable progress has been made in elucidating the neurobiological underpinnings of schizophrenia, its pathophysiology remains only partially understood, and clinical diagnosis continues to rely predominantly on subjective symptom assessment rather than objective biomarkers (4).

Interoception—the sensing, interpretation, and integration of internal bodily signals—has emerged as a central construct in contemporary psychiatry and neuroscience. Interoceptive processing involves hierarchical neural systems that encode and integrate visceral and physiological signals to generate dynamic representations of the internal bodily state. Primary interoceptive signals are conveyed via spinal and vagal afferent pathways to the posterior insular cortex, where they are represented in a modality-specific manner. These signals are subsequently integrated in higher-order regions, including the anterior insula and anterior cingulate cortex, which support emotional awareness, self-referential processing, and adaptive regulation of behavior. Through this hierarchical integration across distributed neural circuits, interoception contributes to emotional regulation, self-awareness, decision-making, and adaptive functioning (5, 6). Recent theoretical frameworks, including predictive coding models, propose that interoception arises from hierarchical inference processes integrating sensory signals with prior expectations about bodily states (7, 8).

Interoceptive functions can be examined through validated behavioral paradigms, such as the heartbeat counting task (HCT) (9), as well as through subjective self-report measures, including the Multidimensional Assessment of Interoceptive Awareness (MAIA) and the Body Perception Questionnaire (BPQ) (10, 11). Although the heartbeat counting task (HCT) is one of the most widely used paradigms for assessing interoceptive accuracy, its construct validity has been increasingly debated in recent literature. Several studies have suggested that HCT performance may be influenced not only by interoceptive ability itself but also by factors such as beliefs about heart rate and time estimation ability (12–14). Despite these limitations, the HCT remains widely used in psychiatric and schizophrenia research, allowing comparability with previous studies. To address potential confounding effects related to temporal perception, the present study additionally includes a time estimation task and will account for time estimation performance in the statistical analysis.

Growing research suggests that altered interoceptive processing may contribute to the disturbances in bodily self-awareness and affective dysregulation observed in schizophrenia (15, 16). Our recent systematic review and meta-analysis (17) provided comprehensive quantitative evidence demonstrating significant and consistent impairments in both interoceptive accuracy and interoceptive sensitivity in individuals with schizophrenia. These findings establish interoceptive dysfunction as a robust and measurable feature of schizophrenia and highlight its relevance to broader disturbances in bodily self-awareness, emotional processing, and self–other differentiation (18, 19). However, despite strong behavioral evidence, the neural mechanisms underlying interoceptive impairments in schizophrenia remain insufficiently understood. In particular, few studies have directly examined the relationships between behavioral interoceptive performance and alterations in functional and structural brain networks implicated in interoceptive processing (20–22).

Taken together, current evidence highlights interoception as a promising but understudied dimension of psychopathology in schizophrenia. Although behavioral and subjective interoceptive impairments have been documented, the neurobiological mechanisms that give rise to these abnormalities remain largely unknown. Although interoceptive processing has been linked to a distributed set of brain regions, the specific functional and structural substrates of interoceptive impairments in schizophrenia remain insufficiently characterized. Functional MRI studies have consistently implicated the insular cortex as a core hub, with the posterior insula supporting primary interoceptive representations and the anterior insula integrating interoceptive signals with salience processing and affective evaluation. Additional regions frequently involved include the anterior cingulate cortex (ACC), somatosensory cortex, thalamus, and prefrontal areas, reflecting integration of visceral signals with attention, emotion, and self-related processing. In parallel, DTI research suggests that interoceptive functions rely on the integrity of white-matter pathways connecting these regions, including thalamocortical projections and fronto-limbic association tracts (e.g., cingulum bundle and uncinate fasciculus), which may support communication between insula/ACC hubs and distributed cortical networks. However, it remains unclear how alterations in intrinsic brain activity, functional connectivity, and white-matter microstructure across these interoception-related systems jointly contribute to behavioral interoceptive deficits in schizophrenia (23, 24). A multimodal approach integrating behavioral assessment, self-report measures, and neuroimaging is therefore essential to advance mechanistic understanding in this area.

To address this gap, the present study proposes a comprehensive investigation of interoceptive dysfunction in schizophrenia using validated behavioral paradigms and a multimodal MRI framework. By examining intrinsic neural activity (rs-fMRI), connectivity patterns, and structural integrity (Diffusion Tensor Imaging, DTI), alongside standardized symptom ratings and cognitive assessments, this study aims to identify neural correlates of interoceptive dysfunction and clarify their associations with clinical features. Findings from this research may provide mechanistic insight into bodily self-disturbance in schizophrenia and contribute to the development of objective biomarkers and future interoception-focused intervention strategies.

## Methods

2

The overall workflow of participant recruitment, assessment procedures, and MRI acquisition is illustrated in **Figure 1**.

**Figure 1 f1:**
[figure not shown]
Study workflow. Overview of participant recruitment, eligibility screening, behavioral and clinical assessments(PANSS, HAM-A, HAM-D, TMT, DSST, AFT), interoception tasks (HCT, MAIA, BPQ, Time Estimation Task), MRI acquisition, and data preprocessing.

### Objectives

2.1

#### Primary objectives

2.1.1

To compare interoceptive accuracy between individuals with schizophrenia and matched healthy controls using the heartbeat counting task (HCT).To examine group differences in subjective interoceptive awareness using validated self-report instruments, including the MAIA and the BPQ.

#### Secondary objectives

2.1.2

To investigate associations between interoceptive impairments (behavioral and subjective) and clinical symptom severity, including positive, negative, and general psychopathology (Positive and Negative Syndrome Scale, PANSS), as well as comorbid anxiety and depression (Hamilton Anxiety Scale, HAM-A, Hamilton Depression Scale HAM-D).To evaluate relationships between interoceptive accuracy and cognitive performance, including processing speed (Digit Symbol Substitution Test, DSST), executive functioning (Trail Making Test, TMT), and verbal fluency (Animal Fluency Test).

#### Exploratory objectives

2.1.3

To characterize abnormalities in intrinsic neural activity within interoception-related regions (e.g., anterior insula, anterior cingulate cortex, amygdala, thalamus) using resting-state fMRI metrics such as amplitude of low-frequency fluctuations (ALFF), regional homogeneity (ReHo), and functional connectivity.To assess structural alterations in white-matter pathways implicated in interoceptive processing using DTI indices, including fractional anisotropy (FA), mean diffusivity (MD), radial diffusivity (RD), and axial diffusivity (AD).To examine brain–behavior associations by linking neural abnormalities with interoceptive accuracy, subjective interoceptive awareness, clinical symptoms, and cognitive performance.To evaluate performance on a time estimation task and explore its associations with interoceptive accuracy, subjective interoceptive awareness, clinical symptoms, and cognitive functioning.To identify potential multimodal neural markers of interoceptive dysfunction in schizophrenia.

### Study design

2.2

This study adopts a cross-sectional, observational design comparing individuals with schizophrenia and matched healthy controls. All participants will undergo standardized assessment procedures, including behavioral interoceptive tasks, subjective questionnaires, clinical symptom ratings, cognitive tests, and multimodal MRI scanning. The study procedures follow a fixed sequence to ensure consistency across participants. Data collection is conducted at Wuxi Mental Health Center. The study protocol has received ethical approval from the institutional review board and has been registered in the Chinese Clinical Trial Registry (ChiCTR2500110551).

### Participants

2.3

Participants will include 30 individuals with schizophrenia and 30 age- and sex-matched healthy controls. The planned sample size was informed by effect sizes reported in our recent meta-analysis examining interoceptive accuracy in schizophrenia (17). That study reported a moderate effect size for group differences in interoceptive accuracy between individuals with schizophrenia and healthy controls. Based on this effect size, a sample of approximately 30 participants per group provides adequate statistical power (approximately 80%) to detect group differences at an alpha level of 0.05. In addition, sample sizes of approximately 25–35 participants per group are commonly reported in multimodal neuroimaging studies investigating schizophrenia. Therefore, the present sample size was considered appropriate for the behavioral objectives of this study.

Individuals with schizophrenia will be recruited from inpatient and outpatient units at Wuxi Mental Health Center and diagnosed by two senior psychiatrists according to DSM-5 criteria. Healthy controls will be recruited from the local community through advertisements and word-of-mouth and screened To ensure the absence of psychiatric, neurological, or major medical conditions. All participants will be right-handed, aged 18–65 years, and capable of providing written informed consent.

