#### Primary outcome

2.5.1

Interoceptive accuracy, assessed using the heartbeat counting task (HCT).

Interoceptive accuracy will be quantified using the standard HCT formula across the three intervals(25 s, 35 s, 45 s).

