#### Behavioral and questionnaire data

2.6.1

All behavioral, clinical, and questionnaire analyses will be performed using SPSS 26.0 and R 4.3.0.Group comparisons: Continuous variables (HCT accuracy, time estimation performance, MAIA, BPQ, TMT, AFT, DSST) will be compared using independent-samples t-tests or Mann–Whitney U tests for non-normal distributions. Categorical variables will be analyzed using χ² tests.All analyses will control for age, sex, years of education, and medication dosage (chlorpromazine equivalents). In analyses involving HCT accuracy, time estimation performance will additionally be included as a covariate to control for potential confounding effects related to temporal estimation ability. Additional sensitivity analyses will examine whether group differences in HCT accuracy remain significant after controlling for time estimation performance.Correlation analyses: Within each group, associations between interoceptive accuracy, subjective measures (MAIA/BPQ), PANSS scores, and cognitive performance will be examined using Pearson or Spearman correlations with FDR correction.

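### Thirty per group gives the stated 80% power only if the unquantified moderate effect is about d = 0.74 (two-sided); at the conventional d = 0.5 it gives about 48%

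*Protocol article*

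**What the plan says.** The planned sample is fixed in section 2.3 (Participants): "Participants will include 30 individuals with schizophrenia and 30 age- and sex-matched healthy controls". The justification runs in three steps. The input comes from the study group's own meta-analysis: "That study reported a moderate effect size for group differences in interoceptive accuracy between individuals with schizophrenia and healthy controls". The output is derived from it: "a sample of approximately 30 participants per group provides adequate statistical power (approximately 80%) to detect group differences at an alpha level of 0.05". The conclusion is that "the present sample size was considered appropriate for the behavioral objectives of this study".

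Section 2.5.1 makes heartbeat counting task (HCT) accuracy the single primary outcome. For the group comparison, section 2.6.1 lists HCT accuracy among the continuous variables that "will be compared using independent-samples t-tests or Mann–Whitney U tests for non-normal distributions". The same section says analyses will control for age, sex, education and medication dose, and for time estimation where HCT is involved.

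Section 2.3 gives no numerical effect size, no confidence interval for it, no sidedness and no allowance for attrition. The Discussion acknowledges a modest sample, but it limits that warning to subtle neural effects and to individual-level or subgroup analyses. The behavioural primary outcome is not covered by it.

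**The concern.** Section 2.3 presents the power figure as a consequence of the effect size, so the two should agree. On the ordinary use of the word, a moderate standardised difference is about half a standard deviation, and 30 per group is well short of what that needs for 80% power. This is the only power statement for the primary outcome. The supporting remark about 25 to 35 participants per group refers to imaging studies and says nothing about power for HCT accuracy. A reader who takes the 80% at face value could give a non-significant HCT difference more weight than the design supports, if the real effect is of ordinary medium size.

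**Working it through.** **Inputs**
- n = 30 per group, 1:1 (section 2.3).
- Alpha = 0.05 (section 2.3). Sidedness is not stated; two-sided is taken as the main case and one-sided is also shown.
- Test: independent-samples t-test, or Mann–Whitney U if non-normal (section 2.6.1).
- Effect: described only as moderate. Assumption: d = 0.5, with a range around it.
- Attrition: none stated, none applied.

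**Step 1: try to reproduce the 80%.** In the normal approximation, power = Φ(d·√(n/2) − 1.960). With d = 0.5 and n = 30, 0.5 × √15 = 1.936, and Φ(1.936 − 1.960) = Φ(−0.024) = 0.491. The exact noncentral-t calculation (58 degrees of freedom) gives 0.478. The stated figure is not reproduced at d = 0.5.

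**Step 2: vary the effect** (noncentral t, 30 per group, alpha 0.05).

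| d | Two-sided | One-sided |
|---|---|---|
| 0.40 | 33% | 45% |
| 0.50 | 48% | 61% |
| 0.60 | 63% | 74% |
| 0.65 | 70% | 80% |
| 0.70 | 76% | 85% |
| 0.74 | 80% | 88% |
| 0.80 | 86% | 92% |

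**Step 3: solve for the effect that gives 80%.** The normal approximation is d = (1.960 + 0.842) × √(2/30) = 2.802 × 0.258 = 0.723. Exact values are 0.736 two-sided and 0.650 one-sided. Two-sided power between 78% and 82% corresponds to d between about 0.72 and 0.755.

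**Step 4: solve for n.** For 80% power, two-sided, the exact calculation needs 64 per group at d = 0.5 (63.8 rounded up), 45 at d = 0.6 and 34 at d = 0.7.

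**Step 5: look for another route to 80% at d = 0.5** (two-sided).
- Mann–Whitney, with efficiency 0.955 applied to n: 46%.
- Matched-pairs t-test with within-pair correlation 0, 0.3 or 0.5: 47%, 61%, 75%. The plan names independent-samples tests, so this is shown only for completeness.
- Covariates explaining a share R² of the outcome variance, so that d becomes d/√(1 − R²): 62% at R² = 0.3 and 77% at R² = 0.5. Reaching 80% takes R² = 1 − (0.5/0.736)² = 0.54.

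**Step 6: another meaning of moderate.** If the word referred to a correlation of 0.3, then d = 2 × 0.3/√(1 − 0.09) = 0.63, and power is 67% two-sided or 78% one-sided.

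**The case against.** The strongest reply is that the decisive input is not in the document. The numerical effect is in the cited meta-analysis, and an article may leave such a number to a fuller document. If the pooled estimate were about 0.72 to 0.755, the two-sided 80% would reproduce and only the adjective would be loose. That stands. A reader might infer from the table that the study really has 48% power, or that the design fails to deliver what it promises. The document does not support either statement, because 48% depends on reading moderate as d = 0.5.

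A reader might also infer that no effect short of large gives 80%, or that one-sided testing could not rescue the figure. Neither holds. Some would call anything from 0.5 up to 0.8 moderate, and 0.74 lies inside that range. A one-sided test reaches 80% at d = 0.65. The Abstract's expectation is directional (reduced accuracy in patients), although no one-sided test is stated and the objectives speak of comparing groups.

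Covariate adjustment can also raise power: two-sided, d = 0.7 with R² = 0.10 gives 80%. But the planned adjustment for chlorpromazine-equivalent dose may pull the other way, since dose would be strongly tied to group if controls are coded as zero. The net direction cannot be settled from the document, so it is no basis for either side.

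Finally, nothing in the article says that a null HCT result will be taken as absence of impairment. That is a possible misreading, not a stated plan.

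What remains is narrower than a complaint about missing detail. The article prints an input and a result that disagree on the ordinary reading of the input, and its own caveat about sample size does not extend to the primary outcome.

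**Conclusion.** The point holds in conditional form. At the conventional d = 0.5, 30 per group gives about 48% power two-sided and 61% one-sided, and none of the variants at that effect in steps 1, 2 and 5 comes within two points of 80%. The stated 80% needs d of about 0.74 two-sided or about 0.65 one-sided, well above the usual medium benchmark. The stated power therefore does not follow from the stated input unless the pooled effect is that large.

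This rests on the two-sample t-test, alpha 0.05, no attrition and no covariate adjustment, and on d = 0.5 as the usual meaning of moderate. The arithmetic is certain; the true power is unknown until the pooled effect is printed.

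**What to change.** Keep 30 per group and amend the power statement in section 2.3:
1. Give the pooled effect size for interoceptive accuracy from the meta-analysis, with its confidence interval, and state whether the test is one- or two-sided.
2. Replace the approximate 80% with the power at that value.
3. Add that, for an unadjusted two-sided comparison at 0.05, 30 per group gives 80% power only for d of about 0.74 or more, and about 48% at d = 0.5.

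If the pooled effect does support 80%, printing it resolves the mismatch and only the adjective needs changing. The cost is a few sentences and no extra participants. The downside is that the stated power may become less favourable.

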#### Inclusion criteria (schizophrenia group)

2.3.1

Diagnosis of schizophrenia confirmed by two attending or senior psychiatrists according to DSM-5 criteria.Age between 18 and 65 years.Right-handedness (Right-handedness was required to minimize variability related to hemispheric lateralization of brain structure and function. Hemispheric dominance has been shown to influence functional connectivity patterns, regional activation, and white-matter organization in MRI studies. Restricting the sample to right-handed individuals helps reduce inter-individual variability and improves the interpretability of group-level analyses of functional and structural neuroimaging measures, particularly in regions implicated in interoceptive processing, such as the insula and anterior cingulate cortex).Stable antipsychotic medication regimen for at least two weeks or medication-naïve (status will be recorded for analysis).Ability to understand study procedures and provide informed consent.

#### Exclusion criteria (both groups)

2.3.2

History of neurological disorders, severe head injury, or seizure disorders.Current substance or alcohol use disorder (past 6 months).Major medical or endocrine disorders that may influence interoceptive processing (e.g., severe cardiovascular disease, diabetes with autonomic neuropathy).Pregnancy or breastfeeding.Contraindications to MRI (e.g., implanted metallic devices, severe claustrophobia).Intellectual disability or severe cognitive impairment was assessed using standardized cognitive screening measures, including the Montreal Cognitive Assessment (MoCA), in conjunction with clinical evaluation and functional history.

